# **Protocol NKEBN/8/2010 (last amendment 01.05.2012):**

**Acronym Title:** TregVac

**Clinical Phase:** Phase 1 [classified by the Ethics Committee] **Accrual Objective: 20 [**10 subjects in Tregs arm and 10 subjects in control arm]

**Accrual Period: 12** months **Follow-up Period: 24** months

**Study duration: 36** months

**Place:** Medical University of Gdańsk, Department of Immunology and Department of Pediatrics, Hematology and Oncology; National Blood Bank, Gdańsk Unit

**Study Design:** A prospective, non-randomised pilot study to investigate the safety and efficacy of cellular therapy of recent-onset type 1 diabetes (DM1) with ex vivo expanded CD4+CD25+CD127- T regulatory cells.

**Treatment Description:** Patients will receive a single or double infusions of ex vivo expanded autologous CD4+CD25+CD127- T regulatory cells (Tregs) in a total dose of up to 30x106cells/kg b.w. All the patients will be on standard insulin therapy. (amended 01.05.2012)

**Primary Endpoint:** Success of the treatment will be defined as a proportion of patients with higher C-peptide and lower requirement for exogenous insulin in the treated group in comparison with the control individuals. The key endpoint is:

- The proportion of subjects with no reported adverse effects of the treatment from day 0 to two years after administration of Tregs. The day of Tregs infusion is designated Day 0 (as recommended by the Ethics Committee).
- The proportion of subjects with daily insulin dose (DDI) ≤ 0.5UI/kg b.w. and plasma fasting C-peptide levels more than 0.5ng/mL present without any stimulation at Day 365. The day of Tregs infusion is designated Day 0.

**Secondary Endpoints:** The key secondary endpoints are the following:

1. The proportion of subjects with daily insulin dose (DDI) ≤ 0.5UI/kg b.w. and plasma fasting C-peptide levels >0.5ng/mL present without any stimulation at 120days after the administration of Tregs. The day of Tregs infusion is designated Day 0.
2. The proportion of subjects with daily insulin dose (DDI) ≤ 0.5UI/kg b.w. and plasma fasting C-peptide levels >0.5ng/mL present without any stimulation from Day 0 to two years after the administration of Tregs. The day of Tregs infusion is designated Day 0.
3. The proportion of subjects with ≥15% reduction of DDI/kg b.w. from baseline at 120days after the administration of Tregs. The day of Tregs infusion is designated Day 0.

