        - Functional tests results [can only be performed when indicated by medical conditions of the patients and NOT solely as an efficacy check as recommended by the Ethics Committee]

Safety End Points:

Day of the Treg infusion:

- Assessment of the incidence and severity of immediate Adverse Effects resulted from the administration of Tregs (reactions of the hypersensitivity, embolism) and blood drawing (>2 g/dL decrease in haemoglobin concentration)

14 days following the adoptive transfer of Tregs:

- Assessment of the incidence and severity of possible Adverse Effects resulted from the infusion of Tregs including: viral, bacterial, or fungal infections, and benign or malignant neoplasms,

120 ± 14 days following the adoptive transfer of Tregs:

- Assessment of the incidence and severity of possible Adverse Effects related to the infusion of Tregs including: viral, bacterial, or fungal infections; and benign or malignant neoplasms.

365 ± 14 days following the adoptive transfer of Tregs:

- The incidence and severity of possible Adverse Effects related to the infusion of Tregs including: viral, bacterial, or fungal infections; and benign or malignant neoplasms,

2 years ± 14 days following adoptive transfer of Tregs:

- The incidence and severity of possible Adverse Effects related to the infusion of Tregs including: viral, bacterial, or fungal infections; and benign or malignant neoplasms,

Cessation of the Trial Criteria:

- Any severe Adverse Effect in two or more patients with confirmed link to the administration of Tregs

Inclusion Criteria:

Patients who meet all of the following criteria are eligible for participation in the study:

TREGS STUDY ARM

1. Male and female patients 5 to 18 years of age.
2. Ability to provide written informed consent by parents (and patients if above 16years old)
3. Clinical history of autoimmune type 1 diabetes diagnosed within recent 2 months and presence of at least one type of anti-islet autoantibody: antiGAD, antiIA2, IAA, ICA (high titer),.
4. Fasting plasma C-peptide more than 0.4ng/mL
5. Involvement of the patients and parents in the intensive diabetes management defined as self monitoring of glucose values no less than three times/ day and by the administration of insulin injections each day or insulin pump therapy.
6. Patient and parents mentally stable and able to comply with the procedures of the study protocol.
7. Appropriate venous access for blood drawing.

CONTROL GROUP ARM :

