**B. Procedures**

**All procedures are concordant with ‘the Medical Experiment requirements’ chapter of the Medical Doctor Act (Parliament of the Republic of Poland 1999 with amendments)**

1. **Recruitment**

The recruitment will be performed in the outpatient clinic of the the Department of Pediatrics, Hematology and Oncology Medical University of Gdańsk. Patients and parents will have a chance to discuss the study procedures and options with the recruiting named physician and time to read all necessary information related to the study (attached to this document as information for patients and parents).

1. **Blood drawing**

Recruited patients, after informed consent is signed by the parents, will be admitted to the Department of Pediatrics, Hematology and Oncology Medical University of Gdańsk. Blood will be drawn in the clinic by certified nurse according to the standard operating procedure of the ward for handling of blood samples. The only exception is the need of anastesiologist assistance during the procedure.

The volume of blood drawn will be calculated according to the following algorithm: Maximal volume of blood to be drawn is equal to 1% of the body weight but no more than 250ml [e.g. child weighting 20kg – 200ml of blood is allowed, child weighting 40kg – 250ml of blood is allowed ]. Then it will be separated in the blood bank to buffy coat and plasma and transferred to GMP laboratory [details of the transfer described in standard operating procedures for blood transport of the blood bank] for further processing.

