Patients’ identity will remain confidential throughout the study period unless disclosure is required by law. It has been included in the Informed Consent Form that the data may be shared by study personnel other than the Primary Investigator, representatives of the approved government agencies, the Ethics Committee, and other regulatory agencies. Patients will be identified only by a unique identifier number. All data records and computers containing information about subjects specifically relevant to this study will be maintained in a locked, secured office. All study results for studies performed by hospital laboratories for which the results are posted on the Hospital computer system will be maintained by a secured password system with all the confidentiality safeguards afforded to patients receiving routine, non-experimental care. The results of this study may be published and presented in scientific meetings, however, the patient will not be identified in such publications or presentations.

- 1. **Adverse effects**

Definition of adverse event: any unfavorable and unintended sign (including an abnormal laboratory finding), symptom, or disease temporally associated with the use of a medical treatment or procedure regardless of whether the sign, symptom or disease is considered related to the medical treatment or procedure.

Definition of serious adverse event (SAE): any event that is fatal or life-threatening, that is permanently disabling, requires or extends hospitalization of the subject, represents a significant overdose or breach of protocol, or suggests that a drug or procedure used in a research protocol has produced congenital anomaly or cancer, or, in the opinion of the investigator, represents other significant hazards or potentially serious harm to the research subject or others.

Severity grading scale:

Mild: adverse event of little clinical significance

Moderate: adverse event of mild to severe significance; causing some limitation of usual activities

Severe: see definition of SAE above

Attribution scale:

Not related: clearly not related to the study

Possible: may be related to the study

Probable: likely related to the study

Definite: clearly related to the study

Unable to assess

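### The adverse event scales rate attribution to the study as a whole and equate severe with serious, so they do not fit the safety endpoints and cessation rule that depend on them

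*Protocol*

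**What the plan says.** The synopsis (Protocol, Cessation of the Trial Criteria) has a single criterion: "Any severe Adverse Effect in two or more patients with confirmed link to the administration of Tregs".

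The safety endpoints (Protocol, Safety End Points) ask for incidence and severity. On the day of infusion they cover "immediate Adverse Effects resulted from the administration of Tregs (reactions of the hypersensitivity, embolism) and blood drawing", with a haemoglobin fall of more than 2 g/dL as the marker for blood drawing. At 14 days, 120 days, 365 days and 2 years they concern effects of the Treg infusion. The first key endpoint (Protocol, Primary Endpoint) is "The proportion of subjects with no reported adverse effects of the treatment from day 0 to two years after administration of Tregs".

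The scales that classify events are in section D, under Adverse effects. The attribution scale has five levels: Not related, Possible, Probable, Definite and Unable to assess. The four levels of relatedness all refer to the study; the top two read "Probable: likely related to the study" and "Definite: clearly related to the study". The severity scale has Mild, then "Moderate: adverse event of mild to severe significance; causing some limitation of usual activities", then "Severe: see definition of SAE above". The SAE definition it points to includes hospitalization, a significant overdose, a breach of protocol, and a clause left to the investigator's opinion.

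On blood drawing (section B, Procedures): "Maximal volume of blood to be drawn is equal to 1% of the body weight but no more than 250ml", with an anaesthesiologist assisting.

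**The concern.** The cessation rule and the safety endpoints use two terms, a link to Tregs and severity, that section D should make recordable. Section D records relation to a different object (the study) and uses seriousness as its top severity grade. If the scales are followed as written, the recorded data do not show which events belong to the Treg infusion, and the grade does not describe how intense an event was.

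The safety endpoints of a phase 1 study in children are at stake: a table of incidence and severity built from these two fields would mix two sources of harm, and its severity column would mix intensity with regulatory status. The same fields are what the principal investigator and the Ethics Committee would look at first to see whether the cessation criterion has been met.

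**Working it through.** The protocol states no operating characteristic for the rule, so there is no figure to reproduce. The check is mainly a comparison of texts.

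**Step 1: attribution.** What each provision needs, against what section D records:

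| Provision | Relation needed | Relation recorded |
|---|---|---|
| Cessation rule | to the administration of Tregs | to the study |
| Safety endpoints, 14 days to 2 years | to the Treg infusion | to the study |
| Safety endpoint, day of infusion | to Tregs and to blood drawing, each with its own examples | to the study |
| First key endpoint | to the treatment | to the study |

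Blood drawing is a real second exposure. A 20 kg child may give 200 mL, which is 200 / 20 = 10 mL/kg. A haemoglobin fall of more than 2 g/dL caused by the draw is clearly related to the study, so it is rated Definite. A hypersensitivity reaction to the infused cells is rated Definite too. The attribution field cannot tell them apart.

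**Step 2: severity.** Three cases run through the scale as written:

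- *Clinically severe, but meeting none of the listed SAE criteria.* It is not Severe by definition. Moderate reaches up to severe significance, so that is where it goes, unless the investigator invokes the opinion clause of the SAE definition.
- *Low-grade fever after a batch found to be contaminated.* Section D, Product contamination, sends a child with fever to hospital and sets no temperature threshold. Hospitalization makes it an SAE, and an SAE is graded Severe.
- *Significant overdose or breach of protocol without symptoms.* It is an SAE, hence Severe.

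The first case understates intensity; the other two overstate it.

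**Step 3: what one classification is worth.** The treated arm has 10 patients. One child moved in or out of a treated-arm count changes the proportion by 1 / 10 = 10 percentage points.

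**Step 4: the word confirmed (illustration only).** No text maps it to an attribution level; its plain reading is Definite. To see how far the choice of level could matter, let p be an assumed per-patient risk of an SAE that is Probably or Definitely due to Tregs, s the assumed share of these that counts, and r = p × s. With 10 independent patients,

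P(two or more) = 1 − (1 − r)^10 − 10·r·(1 − r)^9.

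For p = 10% and s = 1: 1 − 0.3487 − 0.3874 = 0.264. For p = 10% and s = 0.5 (r = 5%): 1 − 0.5987 − 0.3151 = 0.086.

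| Assumed p | s = 1 (Probable counts) | s = 0.5 (only Definite counts, half are Definite) |
|---|---|---|
| 1% | 0.4% | 0.1% |
| 2% | 1.6% | 0.4% |
| 5% | 8.6% | 2.5% |
| 10% | 26.4% | 8.6% |
| 20% | 62.4% | 26.4% |
| 30% | 85.1% | 45.6% |

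Both p and s are assumptions. The table shows that the level should be stated; it does not show that either level is wrong.

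**The case against.** The best defence is that the protocol already separates the two sources where it matters. The cessation rule names Tregs, so a harm from blood drawing cannot count towards it. The day-of-infusion endpoint gives blood drawing its own marker. The draw also precedes the infusion by the culture period, usually 7 to 14 days, and the first key endpoint starts at Day 0. Case report forms are not shown, and a narrative may name the cause. Much of this stands: it shows that the distinction is intended and that many events could be assigned correctly by hand. It does not repair the scale. The protocol assesses blood-drawing effects on the day of infusion together with infusion effects, and the only attribution scale it defines has no place to record which one applies.

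On severity, one can say that treating every SAE as Severe is workable, that the opinion clause can catch clinically severe events, and that counting a hospitalized febrile child towards stopping is cautious. For the stopping rule that is fair. For endpoints that report severity it is not, because the grade then no longer measures intensity.

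A reader might infer three stronger things. One is that the cessation rule is too lax because two SAEs judged Probable would not oblige a stop. Read plainly, confirmed means Definite, and whether a phase 1 rule should also count Probable is a judgement, not an error. Another is that the children are left unprotected. Section 3.5.1 makes the Ethics Committee joint safety monitor with the principal investigator, with reporting within 48 hours for fatal or life-threatening events and ten days for all others, and nothing limits stopping to this one criterion. The third is that the firing probabilities measure a defect. They rest on assumed rates and an assumed share. The earlier experience the protocol describes, no side effects in eight patients with a different disease, has a one-sided 95% upper limit of 1 − 0.05^(1/8) = 31%. That fails to exclude high rates but gives no support for them.

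**Conclusion.** The point holds as a mismatch between definitions. Section D attributes events to the study where the endpoints and the cessation rule need the Treg infusion, and its severity scale merges intensity with seriousness and overlaps at Moderate. Both follow from the text and need no event rate. Their effect on results depends on how many events are ambiguous, which the protocol does not allow one to estimate; the only firm size is 10 percentage points per reclassified child in an arm of 10.

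The conclusion assumes that the section D scales are used as written and that no other form records the source of harm. Given the joint monitoring by the Ethics Committee and the separation already present in the safety endpoints, it is a minor correction, but a real one, and it lies in text the protocol itself fixes.

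**What to change.** Amend section D and the cessation criterion together:

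- **Attribution.** Replace the study as the object of the scale with two ratings per event, one for Treg infusion and one for blood drawing, keeping the existing levels.
- **Severity.** Record a mild, moderate or severe intensity grade with non-overlapping definitions, separately from SAE status (yes or no). Use intensity for the endpoints that report severity.
- **Cessation rule.** Word it in recorded terms, for example: an adverse event of severe intensity or an SAE, in two or more treated patients, attributed to the Treg infusion at a named level. The principal investigator and the Ethics Committee choose that level and record the choice. Keeping SAE in the rule means that a hospitalized low-grade fever still counts, which is a cautious choice that can be made openly; adding severe intensity brings in the clinically severe event that is not an SAE.

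The cost is one short amendment, with one added attribution field and one added grade per adverse event. No procedures are added. If the chosen level includes Probable, the trial may stop more readily, by an amount that the protocol's own figures cannot determine.

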| 15. | [name] MD PhD  (Professor of Immunology) | Internal advisor of the programme |

**D. Safety Monitoring for phase I study** (as recommended by the Ethics Committee)

1. **Clinical safety assessments**

Clinical safety will be assessed by physical examination, measurement of vital signs (blood pressure, heart rate, oral temperature and respiratory rate) and occurrence of clinical events such as opportunistic infection and other reportable adverse events. These assessments will be made at regularly scheduled clinic visits at intervals detailed in schema of the follow up.

1. **Product contamination**

Physician notification of Tregs product contamination occurs as dictated by Microbiology Laboratory SOP by direct phone notification of the principal investigator (PI) for positive culture results. The PI’s mobile number is included in the SOP for this protocol, available to technicians in the Microbiology Laboratory.

Upon learning of contamination in a batch already administered, the patient will be contacted by telephone by PI, the nurse coordinator, or another co-investigator, informed of the contamination, and queried regarding symptoms including but not limited to fever, chills, malaise and dizziness. Negative responses will result in verbal reassurance, counseling on signs/symptoms which should prompt the subject to contact our center and/or seek medical assistance, and the addition of a complete blood count (including white blood count and differential) and blood cultures x 2 at the next protocol-scheduled blood draw. Affirmative responses to any of these questions will result in requesting the subject to come immediately to The Medical University of Gdańsk Medical Centre, or, if not possible, to another medical facility for evaluation. Evaluation will include at least history and physical, CBC and blood cultures. Fever, leukocytosis, and/or positive blood cultures will result in hospitalization and the initiation of empirically chosen antibiotics (based on the positive culture results from the product) until the signs/symptoms resolve and/or positively identified organisms with antibiotic sensitivities allow specifically tailored antibiotic therapy.

The fluidics line from infusion is stored for 48 hours and will be sent to the Microbiology Laboratory for assessment when contamination or other adverse effects are reported.

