**3.5.1. Adverse event reporting plan**

The principal investigator, together with the Ethics Committee, will serve as the data safety monitor for this study. The principal investigator will provide interim reports as required to the Ethics Committee, and to the General Pharmaceutical Inspectorate. All fatal or life-threatening events occurring as part of this trial will be reported within 48 hours, even if all the information is not available. Follow-up written notification will be submitted within 10 days. All other adverse events will be reported within ten days.

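### One fatal or life-threatening event caused by Tregs does not meet the only cessation rule, and nothing in the protocol makes the next harvest or infusion wait for a decision

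*Protocol*

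**What the plan says.** The synopsis, under Cessation of the Trial Criteria, gives a single criterion: "Any severe Adverse Effect in two or more patients with confirmed link to the administration of Tregs".

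Section D, Adverse effects, grades the top severity level by cross-reference: "Severe: see definition of SAE above". The definition referred to begins "any event that is fatal or life-threatening, that is permanently disabling, requires or extends hospitalization of the subject" and goes on to other categories. Death has no tier of its own. The attribution scale has five levels: Not related, Possible, Probable, Definite and Unable to assess. The second level reads "Possible: may be related to the study". No level is called confirmed.

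Section 3.5.1 sets out what follows an event. "All fatal or life-threatening events occurring as part of this trial will be reported within 48 hours", with written follow-up within 10 days. On oversight it says "The principal investigator, together with the Ethics Committee, will serve as the data safety monitor for this study" and "The principal investigator will provide interim reports as required to the Ethics Committee, and to the General Pharmaceutical Inspectorate".

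For a contaminated product, Section D says "Upon learning of contamination in a batch already administered, the patient will be contacted by telephone by PI" or by other study staff. Evaluation and treatment follow where indicated. The stored infusion line is tested, and the Ethics Committee is notified (within 48 hours if an SAE results).

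Section D, Consenting process, has the principal investigator judge each candidate's suitability before consent is discussed.

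**The concern.** In a small Phase 1 trial of a cell product in children, a single death or near-death that may be due to the product is normally enough to pause dosing while someone decides whether to go on. Here the stated threshold is two patients, each with a confirmed link. A trial run exactly as written could therefore infuse the next child, or give a second infusion to a child already treated, after one Treg-caused death and before any trial-level decision.

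The protocol itself foresees causes of such an event. It lists hypersensitivity and embolism as immediate effects to assess, and it plans for contamination discovered after a batch has been given. Products are autologous and released one by one, but they share a sorter, media, beads and facility. A fault common to several children is possible, though not certain.

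**Working it through.** The protocol gives no operating figure for this rule, so there is none to reproduce. The point is textual; the arithmetic only scales it.

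**Step 1: does one Treg-caused death meet the rule?** Severe means SAE, and a death is one SAE in one patient. The rule needs two or more patients, and 1 < 2, so it is not met.

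**Step 2: does any other provision hold the next harvest or infusion?**

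| Provision | What it requires | Makes the next child wait? |
|---|---|---|
| 3.5.1, reporting | 48-hour report, 10-day written follow-up, interim reports | No |
| D, Product contamination | Patient contact, evaluation, treatment, line test, notification | No |
| D, Monitoring for toxicity and adverse outcomes | Team review at unspecified intervals | No trigger stated |
| 3.3, Certification of the product | FoxP3, suppression and microbiology tests on that child's product | Only for that child's own product |
| D, Consenting process | Investigator's judgement of each new candidate | Patient-level; does not cover children already enrolled or with cells in culture |

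**Step 3: timing of attribution.** The 48-hour report is due even when information is incomplete, whereas the cessation rule asks for a confirmed link. Confirmation may come after the next infusion is due.

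**Step 4: how often would an infusion fall in the window?** Inputs: 10 treated children, 12 months' accrual, and one or two infusions each (synopsis). Assumption: infusions are spread evenly. Spacing is 365/10 = 36.5 days with one infusion per child. With two, there are 20 infusions in 365 days.

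| Window | One infusion per child | Two per child |
|---|---|---|
| 2 days | 2/36.5 = 0.05 | 2 × 20/365 = 0.11 |
| 10 days | 10/36.5 = 0.27 | 10 × 20/365 = 0.55 |
| 30 days | 30/36.5 = 0.82 | 30 × 20/365 = 1.64 |

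The monitor is usually informed before the next infusion. The 10-day and 30-day rows also give the number of infusions delayed by a pause of that length. Products in a 14-day culture when a pause starts: 14/36.5 = 0.38, or 14 × 20/365 = 0.77 if each infusion has its own culture.

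**Step 5: how often would a pause occur?** The protocol gives no rate. If a proportion p of treated children have a qualifying event, at most 10p pauses are expected. For p = 1%, 5% and 10% (assumed) that is 0.1, 0.5 and 1.0 pauses. At 10 days each they delay 0.03, 0.14 and 0.27 infusions in the whole trial, or 0.05, 0.27 and 0.55 with two per child.

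**Step 6: how often would exactly one linked event occur?** For linked severe events of any kind at an assumed rate p, P(exactly one in 10) = 10p(1−p)^9. This gives 9.1% at p = 1%, 31.5% at 5% and 38.7% at 10%. Fatal or life-threatening events are a subset, so these figures show only that a lone event is an ordinary way for a 10-child trial to unfold. They do not measure the effect of the proposed pause.

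**The case against.** The strongest reply is that nothing stated is wrong. The two-patient rule governs permanent cessation, and what is missing is a separate temporary pause. Every fatal or life-threatening event must be reported within 48 hours whatever its attribution. The monitor can stop the trial at any time, and half of that monitor (the principal investigator) judges each newly recruited child. The safety section was written on the Ethics Committee's recommendation. The timing figures show that the monitor will nearly always know before the next infusion. SOPs and statutes to which the protocol refers are not shown and may require a hold. The pause would also be triggered by events rated Possible, in children whose diabetes can cause complications of its own.

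Much of this stands, and it limits the size of the point. It does not supply the missing requirement: being informed and being allowed to stop are not the same as having to decide before the next child is infused. The investigator's judgement of a new candidate does not reach children already enrolled.

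Two stronger readings should be resisted. A reader might infer that up to nine more children would be infused after a death in the first child (10 − 1 = 9). That is a ceiling: it needs no second linked severe event and no action by the investigator, the Ethics Committee or the inspectorate for the rest of the trial, which nothing in the protocol suggests. A reader might also turn the earlier graft-versus-host experience (no side effects in eight patients) into evidence of danger, since its one-sided 95% upper limit is 1 − 0.05^(1/8) = 31%. That limit concerns any side effect in another disease and shows only that eight patients are few.

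**Conclusion.** The point holds as the absence of a mandatory hold, not as an absence of oversight. In the protocol as available, one Treg-caused fatal or life-threatening event does not meet the cessation rule, and no other provision makes the next harvest or infusion wait for a trial-level decision. The practical exposure is modest: on even accrual, about 0.05 to 0.11 infusions fall due before the 48-hour report and 0.27 to 0.55 before the 10-day follow-up. A responsible team would probably pause in any case. The change is still worth making, because the consequence could be grave, the participants are children, and the remedy is one sentence. A hold on dosing governs trial conduct and belongs in the protocol beside the cessation rule, so it is not a matter for a statistical analysis plan. The conclusion assumes that no SOP or statute outside the text already imposes a hold; if one does, the protocol need only refer to it.

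**What to change.** Keep the two-patient cessation rule unchanged and add by amendment:

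*Any single fatal or life-threatening event rated Possible, Probable, Definite or Unable to assess in relation to Treg infusion pauses new harvests and infusions until the principal investigator and the Ethics Committee have reviewed it in writing. The target date is that of the 10-day written follow-up. An event rated Not related does not pause the trial.*

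The wider attribution applies only to the pause, because a link can seldom be confirmed within 48 hours. No new committee is needed.

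The costs arise only if such an event occurs:

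- **Delay.** A 10-day pause delays about 0.27 to 0.55 infusions, sometimes for an event later found unrelated.
- **Lost product.** On average 0.38 to 0.77 products are in culture when a pause starts. Culture ends by day +13 and the cells must be given within an hour of release, so a product may be lost. A repeat harvest would mean another draw of up to 250 ml, and the protocol makes no provision for one.
- **Eligibility.** A child awaiting recruitment could pass the 2-month limit since diagnosis.
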